### Sample size estimation

Sample size calculation was performed using PASS 2021 software (NCSS, USA) based on a previous study [24,25] and our preliminary data, with the goal of ensuring adequate power for both co-primary endpoints.

For the 48-hour moderate-to-severe pain incidence (dichotomized NRS): Based on our preliminary dose-finding results, the incidence of moderate-to-severe pain at 48 h was assumed to be 15% for Group A (66 mg), 25% for Group B (44 mg) and 35% for Group C (33 mg). Without optimized long-acting regional analgesia, approximately 74.3% of patients experience moderate-to-severe pain following arthroscopic rotator cuff repair [24,25]. Assuming 1-β = 0.8, α = 0.05 and *R* = 1, 84 participants per group are required.

For the co-primary outcome of cumulative 0–48 h opioid consumption (MME, continuous): Based on our preliminary data and published literature, the mean cumulative MME within 0–48 h was assumed to be 20 mg (SD = 12) in Group A, 35 mg (SD = 12) in Group B and 50 mg (SD = 12) in Group C. Using one-way ANOVA for three-group comparison with α = 0.05 and power = 0.8, 72 participants per group are required.

The larger requirement (84 per group) was adopted to provide ≥80% power for each co-primary endpoint. To allow for a 10% dropout rate, we will enrol 94 patients per group, resulting in a total sample size of 282 participants.

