### Primary and secondary outcomes

The co-primary outcomes will be (1) Rest pain NRS score at 48 h post‑surgery; (2) Cumulative opioid consumption within 0–48 h after surgery, converted to oral morphine milligram equivalents (MME). Secondary outcomes will be (1) Rest pain NRS scores at 6 h, 24 h and 72 h post‑surgery; (2) Muscle Balance Scale (MBS) ratings at 6 h, 24 h, 48 h and 72 h; (3) Motor nerve block assessed by the Bromage score at 6 h, 24 h, 48 h and 72 h [23]; (4) American Shoulder and Elbow Surgeons (ASES) functional score at the same intervals (Table 1); (5) Quality of Recovery-15 (QoR-15) score at 24 h and 48 h post‑surgery.

**Table 1. t0001:** The American shoulder and elbow surgeons (ASES) score.

Activity	Unable to do Score = 0	Very difficult to do Score = 1	Somewhat difficult Score = 2	Not difficult Score = 3
Do usual work				
Do usual sport				
Put on a coat				
Sleep on your painful or affected side				
Wash back/do up bra in back				
Manage toileting				
Comb hair				
Reach a high shelf				
Lift 4.5kg above shoulder				
Throw a ball overhand				
Total scores				

A patient-reported subjective rating system was employed to assess the score, comprising two components: pain (50%) and functional capacity (50%), with a total possible score of 100. Higher scores indicate superior shoulder function.

Specific scoring method: pain score = (10-NRS score) *5; Functional score = total score of 10 items *5/3.

ASES score = pain score + function score.

Although liposomal bupivacaine provides analgesia lasting up to 72 h, its most stable and clinically consistent effect occurs within the first 48 h after surgery. This period also represents the critical window for early postoperative rehabilitation, opioid consumption and acute pain control. Therefore, 48 h was selected as the primary time point to capture the most clinically meaningful analgesic difference among groups, while 72 h was retained as a secondary outcome to assess the extended duration of action.

NRS scores range from 0 (no pain) to 10 (worst imaginable pain). Mild pain (1–3) is non‑disruptive to sleep, moderate pain (4–6) mildly disrupts sleep and severe pain (7–9) prevents or awakens from sleep.

The MBS assesses elbow and wrist flexion strength using a 5‑point scale: 0 (no muscle activity), 1 (slight movement), 2 (movement against gravity only), 3 (movement against resistance with reduced strength) and 4 (strong movement against resistance).

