### Statistical analysis

Normally distributed continuous variables will be presented as mean ± standard deviation (SD), non-normally distributed variables as median (interquartile range, IQR) and categorical variables as number (percentage).

For outcomes assessed at multiple time points, a linear mixed model for repeated measurements (MMRM) will be employed, with fixed effects including group, time point and the group × time interaction, patient as a random intercept, and pairwise comparisons between groups adjusted using Tukey’s correction. Missing data in repeated-measures analyses will be handled under the assumption of missing at random (MAR) using maximum likelihood estimation. The MMRM model naturally accommodates missing data without pre-imputation. A sensitivity analysis using multiple imputation will be conducted to test the robustness of results.

For single time point analyses, normally distributed continuous variables will be compared using one-way ANOVA, followed by post‑hoc pairwise comparisons with Tukey’s correction; non-normally distributed variables using the Kruskal‑Wallis test; and categorical variables using the chi‑square test or Fisher’s exact test as appropriate. Multivariable linear regression will be used to adjust for potential confounding factors, including age, sex, body mass index (BMI), baseline NRS score and surgical duration. A two-sided *P* value < 0.05 will be considered statistically significant.

For the trial to be declared positive regarding the primary hypothesis, both co-primary endpoints must reach statistical significance. Specifically, for at least one pairwise comparison, a statistically significant difference must be observed in both the 48-hour resting pain NRS score and the cumulative 0–48 h MME consumption, after applying Tukey’s correction for multiple comparisons within each endpoint. No additional alpha adjustment (e.g. Bonferroni) will be applied across the two co-primary endpoints. According to ICH E9 guidelines for co-primary endpoints, when a trial requires statistical significance on all co-primary endpoints to declare a positive result, the family-wise error rate is inherently controlled without further adjustment. This principle applies here, as both endpoints must demonstrate improvement to define a clinically successful analgesic regimen.

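### The 84 per group that fixes N is calculated for a dichotomised pain incidence, so 80% power is not shown for the co-primary actually named and tested, the 48 h NRS score

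*Protocol article*

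**What the plan says.** The outcomes section of the protocol article defines the pain co-primary on the 0–10 scale: "The co-primary outcomes will be (1) Rest pain NRS score at 48 h". The abstract says the same. The statistical analysis section makes success depend on that score: "for at least one pairwise comparison, a statistically significant difference must be observed in both the 48-hour resting pain NRS score", together with MME, after Tukey's correction within each endpoint.

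The sample size section works on a different variable. The pain paragraph opens "For the 48-hour moderate-to-severe pain incidence (dichotomized NRS", and the incidence "was assumed to be 15% for Group A (66 mg), 25% for Group B (44 mg) and 35% for Group C (33 mg". With "Assuming 1-β = 0.8, α = 0.05 and" equal allocation it arrives at 84 per group. No test and no pair of groups are named in that paragraph. The MME paragraph assumes means of 20, 35 and 50 mg with SD 12, names a three-group ANOVA, and arrives at 72 per group. The section concludes: "The larger requirement (84 per group) was adopted to provide ≥80% power for each co-primary endpoint". A 10% dropout allowance then gives 94 per group and 282 in total.

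No dichotomised pain outcome appears among the primary or secondary outcomes or in the assessment schedule (Table 3), and no analysis of one is described.

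**The concern.** The only figure that drives N belongs to an endpoint the trial does not list or test, yet it is offered as the power of the endpoint it does test. An incidence calculation says little about a comparison of mean scores unless the score distribution is also specified. The sample size section gives no mean, difference or SD on the NRS scale, so a reader cannot recover the power of the pain co-primary.

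This matters more than usual because both co-primaries must succeed in the same pair of groups. If one is powered almost to certainty, the chance of a positive trial is governed by the other, which here is the one with no stated power.

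**Working it through.** **Inputs.** Rates 15/25/35%, alpha 0.05, power 0.80, MME 20/35/50 mg with SD 12, and 84 per group are from the sample size section. Two-sided testing at 5% and the Tukey rule are from the statistical analysis section. The cut-off NRS ≥ 4 follows from the outcomes section, which grades 4–6 as moderate. All NRS distributions and SDs below are assumptions. The 48 h contrast is treated as a comparison of three means with 84 evaluable per group.

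**1. Where 84 comes from.** Two proportions, A versus C, unadjusted:

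- n = [1.960·√(2 × 0.25 × 0.75) + 0.842·√(0.15 × 0.85 + 0.35 × 0.65)]² / 0.20² = (1.200 + 0.501)² / 0.04 = 72.4, so 73.
- With continuity correction: (72.4/4)·[1 + √(1 + 4/(72.4 × 0.20))]² = 82.1, so 83.
- Fisher's exact test for A versus C has 82% power at 84.

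The stated figure is thus approximated by an unadjusted comparison of the two extreme groups. A three-group chi-square does not give it. The noncentrality is 84 × (0.10² + 0² + 0.10²)/(0.25 × 0.75) = 8.96, which on 2 df gives 76.9% power; 91 per group are needed for 80%. The dropout step reproduces: 84/0.9 = 93.3, so 94.

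**2. MME at 84 per group.** The Tukey critical value for three groups on 249 df is 2.358 on the t scale. For adjacent doses the standardised difference is 15/12 = 1.25, with noncentrality 1.25 × √(84/2) = 8.10. Power exceeds 99.9% for every pair. (The stated 72 per group does not follow from these inputs, which need far fewer. That is a separate matter.)

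Because MME is near certain in every pair, the power of the rule requiring both endpoints in the same pair is essentially the power of the NRS score.

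**3. NRS score, whole-distribution shift (assumption).** Treat the score as normal with common SD and place 15%, 25% and 35% above one cut-off. The normal quantiles are −1.036, −0.674 and −0.385. Noncentrality is d × √42, compared with 2.358:

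| Pair | d (SD) | d × √42 | Tukey power |
|---|---|---|---|
| A–C | 0.651 | 4.22 | 97% |
| A–B | 0.362 | 2.35 | 50% |
| B–C | 0.289 | 1.87 | 32% |

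Simulations of 10,000 trials each, using integer scores limited to 0–10 and matched to the same rates, give 94–96% for A–C with rounded normal scores (SD 1.5 to 2.5), 93% with Poisson and 92% with negative binomial scores.

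**4. NRS score, difference confined to the cut-off (assumption).** Here the groups differ only in the share at or above 4, with the same scores within each side:

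| Scores below / at or above the cut-off | A–C | Any pair |
|---|---|---|
| 0–3 / 4–6 | 55% | 59% |
| 3 / 4 | 76% | 78% |
| 0–3 / 4 | 47% | 51% |

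In every scenario in steps 3 and 4, adjacent-pair power is about 50% or lower.

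**5. What 84 per group can detect.** Solving for 80% Tukey power in one pair gives d = 0.494 (0.494 × √42 = 3.20, and 3.20 − 2.358 = 0.84). That is 0.74, 0.99 and 1.24 NRS points for an assumed SD of 1.5, 2 and 2.5.

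**The case against.** A reader might infer that the trial is underpowered, or that the 80% claim is false. The document does not support that. Success needs only one pair, MME is amply powered, and if the stated rates reflect a general shift in pain scores, A versus C has well over 80% power on the NRS score. The low adjacent-pair figures do not refute the claim either: the sample size section does not promise 80% for every pair and the success rule does not require it. They bear on how well the trial can separate neighbouring doses.

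A reader might also call 84 an arithmetic error. The pain paragraph names no test, so the three-group chi-square is one reading of it; on an A versus C reading, 84 is close to right. The fault lies in the endpoint and in the unnamed test and pair.

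These objections stand, and they limit the conclusion. They do not remove the mismatch. The favourable 97% depends on a distributional assumption the protocol does not make, and other distributions with the same three rates give less than 80%. Nor is this detail that a fuller analysis plan would be expected to supply: the article itself presents a calculation and draws a conclusion from it that does not follow.

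**Conclusion.** The concern holds in this form: at least 80% power is not shown for the 48 h NRS co-primary, because the calculation that sets N concerns another variable and no NRS difference or SD is given. For MME the claim is met by a wide margin on the stated inputs. For the NRS score, A versus C power at 84 per group runs from about 92–97% under whole-distribution shifts to 47–76% when the groups differ only at the cut-off. All of these figures rest on assumed distributions matched to 15/25/35%. The mismatch itself rests on no assumption and can be read directly from the text.

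**What to change.** Keep N = 282. Replace the incidence paragraph with a calculation for the 48 h rest NRS score under the declared Tukey-adjusted comparison. Suitable wording: 84 evaluable participants per group give 80% power to detect a pairwise difference of about 0.49 SD after Tukey adjustment, with the corresponding NRS difference from the preliminary SD. State the power for A–C, A–B and B–C from the preliminary NRS means and SDs, and limit the 80% statement to the endpoint and pair for which it holds.

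Alternatively, make the incidence of NRS ≥ 4 the co-primary, with a matching test and multiplicity rule, and restate its power. That changes a primary endpoint and would have to be carried through the outcomes, the analysis section and the registry record.

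The first option costs one rewritten paragraph and no extra patients. Its downside is that the stated power will look less favourable for adjacent doses, which matters to a trial that aims to choose among three.

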### Randomization and blinding

An independent research coordinator, who will not be involved in the subsequent study, conducted the online randomization using a 1:1:1 allocation ratio and a permuted block size of 3. Subjects will be allocated to either Group A (liposomal bupivacaine 66 mg), Group B (liposomal bupivacaine 44 mg) or Group C (liposomal bupivacaine 33 mg) based on a random sequence (Figure 1). The doses were selected based on the following rationale. Notably, these dose selections remain partly exploratory, as robust pharmacodynamic and dose-response data for liposomal bupivacaine specifically in the superior trunk block (STB) are currently lacking. Nonetheless, the FDA-approved dose for interscalene block (ISB) is 133 mg. ISB targets the C5-C7 nerve roots at the interscalene groove. In contrast, STB is performed more caudally and laterally at the convergence of the C5 and C6 nerve roots, where they form the superior trunk of the brachial plexus. At this location, STB maintains comparable analgesia while allowing for lower local anaesthetic doses. Accordingly, we selected 66 mg (50% of the ISB dose) as the high-concentration group for STB. Second, 33 mg (25% of the ISB dose) was chosen to explore the minimal effective concentration. Third, 44 mg, the midpoint between 33 mg and 66 mg, was selected to identify the optimal balance between analgesia and motor function preservation. This trial is therefore designed to define the optimal concentration for STB. Allocation concealment will be ensured through the use of identical opaque sealed envelopes. An independent anaesthesia nurse at each study centre will be responsible for preparing the study medications. Given that varying concentrations of liposomal bupivacaine exhibit distinct appearances, we will maintain blinding for the surgeons and operating room staff by transferring the medication into identical opaque syringes, labelled solely with the patient’s identification number. The STB procedures will be conducted by a qualified anaesthesiologist, who will not participate in anaesthesia management or the supervision of postoperative care. All additional perioperative clinical care will adhere to the standard practices of the institution. Pertinent data will be documented in the trial case report form (CRF).

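### The 84 per group fits only an unadjusted 66 mg versus 33 mg comparison of dichotomised pain; the pain contrasts involving 44 mg fall well short of 80% power

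*Protocol article*

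**What the plan says.** The Sample size estimation section of the Protocol article sizes the pain endpoint on a dichotomised NRS, with assumed rates of moderate-to-severe pain at 48 h of "15% for Group A (66 mg), 25% for Group B (44 mg) and 35% for Group C (33 mg"). It then states: "Assuming 1-β = 0.8, α = 0.05 and *R* = 1, 84 participants per group are required". Neither the test nor the contrast behind 84 is named. A separate three-group ANOVA calculation for opioid consumption (MME) gives 72 per group, and the section concludes: "The larger requirement (84 per group) was adopted to provide ≥80% power for each co-primary endpoint". Adding 10% for dropout gives 94 per group, 282 in all.

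The Statistical analysis section uses two-sided tests at 0.05 and calls the trial positive when, "for at least one pairwise comparison, a statistically significant difference must be observed in both the 48-hour resting pain NRS score" and in cumulative MME, with Tukey's correction within each endpoint. The Randomization and blinding section says that the 44 mg dose "was selected to identify the optimal balance between analgesia and motor function preservation".

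**The concern.** The trial aims to identify an optimal concentration, and 44 mg is the arm chosen to locate it. To place 44 mg on pain one has to compare it with 66 mg and with 33 mg. The assumed differences there are 10 percentage points each, half the 20 points between the outer arms. A number sized on the outer contrast leaves both inner contrasts weakly powered.

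The success rule needs the same pair to be significant on both endpoints, so strong power on MME cannot make up for weak power on pain. At stake is how a non-significant 66 versus 44 mg result is read. With low power it is a likely result even if the assumed loss of analgesia is real, and beside better motor scores it could be mistaken for equal pain relief.

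**Working it through.** **Inputs.** From Sample size estimation: rates 0.15 (A, 66 mg), 0.25 (B, 44 mg), 0.35 (C, 33 mg); power 0.80; α 0.05; 84 evaluable per group; MME means 20, 35, 50 with SD 12. From Statistical analysis: two-sided tests, Tukey for three pairs.

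**1. Where 84 comes from.** Two groups, two-sided 0.05, 80% power, A versus C, with p̄ = 0.25 and p1(1−p1) + p2(1−p2) = 0.1275 + 0.2275 = 0.355:
- Unpooled: n = (1.960 + 0.842)² × 0.355 / 0.20² = 69.7, so 70.
- Pooled: n = [1.960√(2 × 0.25 × 0.75) + 0.842√0.355]² / 0.20² = 72.4, so 73.
- With continuity correction: (72.4/4) × [1 + √(1 + 4/(72.4 × 0.20))]² = 82.1, so 82 or 83 by rounding.

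The last is within two patients of 84, and R = 1 is two-group notation. A one-sided Bonferroni calculation for the same pair gives 82, but it conflicts with the stated two-sided test. The other pairs come nowhere near: A versus B needs 250 and B versus C 329 (pooled, unadjusted). The dropout step reproduces: 84/0.9 = 93.3, so 94.

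**2. Three-group chi-square on the same rates.**
- w² = [(0.10² + 0 + 0.10²)/3] / (0.25 × 0.75) = 0.0356.
- Noncentrality at n = 84: 252 × 0.0356 = 8.96 on 2 df; power 76.9% (78.2% by simulation).
- By the noncentral chi-square, 90 per group gives 79.8% and 91 gives 80.3%.

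**3. Pairwise power under Tukey, binary endpoint.** Critical value 3.314/√2 = 2.344. Power = Φ(d/SE − 2.344), SE = √{[p1(1−p1) + p2(1−p2)]/84}:
- 66 vs 33 mg: SE 0.0650, d/SE 3.076, power 77% (75% with a pooled null variance); unadjusted 86-87%.
- 66 vs 44 mg: SE 0.0612, d/SE 1.633, power 24% (23% pooled); unadjusted 37%.
- 44 vs 33 mg: SE 0.0703, d/SE 1.423, power 18% (17% pooled); unadjusted 29-30%.

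For 80% under Tukey, n = (2.344 + 0.842)² × variance sum / d², which is about 90, 320 and 421 per group (94, 324 and 425 pooled). The Tukey 95% half-width for 66 vs 44 mg is 2.344 × 0.0612 = 0.144, about 14 points, wider than the assumed 10.

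**4. If the NRS score is analysed as continuous.** The article gives no mean or SD for it, so this step rests on an added assumption: normal scores with a common SD whose proportions above the cut-off are 15%, 25% and 35%. The standardised means are then −1.036, −0.674 and −0.385, giving differences of 0.651 (66 vs 33 mg), 0.362 (66 vs 44 mg) and 0.289 (44 vs 33 mg). With SE = √(2/84) = 0.154 and Tukey's correction, power is about 97%, 50% and 32%. Power for at least one significant pair is also about 97%.

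**5. MME.** Neighbouring means differ by 15 with SD 12, so d/SE = 15/(12 × 0.154) = 8.1. Power exceeds 99.9% for every pair at 84 per group. Pain is therefore the limiting endpoint for any claim about 44 mg.

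**The case against.** The strongest reply is about scope. The co-primary outcome and the success rule are stated on the NRS score; the dichotomised version appears only in the sizing, and the article attaches Tukey to the mixed model and the ANOVA, not to proportions. So the 18-24% is not the power of the planned primary analysis, and that power cannot be computed from the article without an assumption. This stands. It is why both sets of figures are needed; on either set the 44 mg contrasts stay well below 80%.

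Next, the success rule needs only one pair, and the article makes no specific power claim for the 44 mg contrasts. Also true: under the continuous assumption the rule is well powered on pain. But the general claim of at least 80% on each co-primary rests, for pain, wholly on binary rates that do not deliver it at 84 per group, and the article does not say that the inner contrasts were left unpowered.

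The three-group shortfall is 2 to 3 points and would vanish if all 94 per group were evaluable (about 82%). It is minor.

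Finally, the dose choices are described as partly exploratory, and the balance for 44 mg also draws on motor, functional and recovery scores. That is fair, but the pain side of the balance still has to be estimated.

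Two stronger readings go beyond the documents. A reader might infer that a positive trial will usually rest on 66 versus 33 mg alone. In simulation of pain, that holds for about half of positive results with the binary endpoint but only about a quarter under the continuous assumption, so it is not a general statement. A reader might also infer that the plan intends to treat a null 44 mg contrast as equal analgesia. Nothing in the article says so; it is a risk that the text leaves open.

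**Conclusion.** The point holds in this form. The 84 per group is approximately an unadjusted 66 versus 33 mg calculation on dichotomised pain and matches neither the three-group design nor the Tukey rule. On the plan's own rates it gives about 77-78% for the three-group test, 75-77% for 66 versus 33 mg under Tukey, and about 24% and 18% for the two 44 mg contrasts (37% and 30% unadjusted). The alternative figures of 97%, 50% and 32% depend on the normal, common-SD assumption, which the documents neither give nor exclude. The conclusion common to both is that pain evidence on the 44 mg arm falls well short of 80% power, while MME is amply powered for every pair. It does not follow that the trial as a whole is likely to miss its success rule.

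**What to change.** Keep N = 282.

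- **Sample size estimation:** name the contrast and test behind 84. Replace the claim of at least 80% power for each co-primary with the power for the pain endpoint as it will be analysed: about 77% if the binary version is used, or a figure recomputed from a stated mean and SD if the NRS score is kept. State that the 44 mg contrasts on pain are not powered at 80%.
- **Statistical analysis:** report the 44 mg contrasts as differences with Tukey simultaneous 95% confidence intervals. State that a non-significant 44 mg contrast is not evidence of equal analgesia and will not be used to name 44 mg optimal.
- **Optional:** a one-degree-of-freedom dose-trend test as a supportive analysis. On the plan's rates with ordered scores its power at 84 per group is about Φ(√8.96 − 1.96) = 85%.

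The cost is wording in two sections and, if the trend test is taken up, one extra model; no extra patients. The downside is a less favourable stated power and a more limited claim about 44 mg.

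### The printed ≥80% power is not the power of the trial's own success rule; on the stated pain rates that rule has about 78%, and about 17% to 23% for the 44 mg contrasts

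*Protocol article*

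**What the plan says.** Under Sample size estimation, the protocol article sizes the two co-primary endpoints separately.

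- **Pain.** The 48 h endpoint is dichotomised as moderate-to-severe pain, with assumed rates of 15%, 25% and 35% in the 66, 44 and 33 mg groups: "Assuming 1-β = 0.8, α = 0.05 and *R* = 1, 84 participants per group are required". No Tukey step is mentioned.
- **MME.** The assumed means are "20 mg (SD = 12) in Group A, 35 mg (SD = 12) in Group B" and "50 mg (SD = 12) in Group C". The result is: "Using one-way ANOVA for three-group comparison with α = 0.05 and power = 0.8, 72 participants per group are required".

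The two are combined by taking the maximum: "The larger requirement (84 per group) was adopted to provide ≥80% power for each co-primary endpoint". Adding 10% dropout gives 94 per group.

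Under Statistical analysis, the criterion for a positive trial is different: "for at least one pairwise comparison, a statistically significant difference must be observed in both the 48-hour resting pain NRS score and the cumulative" MME, with Tukey's correction applied within each endpoint. Primary and secondary outcomes likewise defines the pain endpoint as the NRS score, not as the proportion above a cut-off.

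**The concern.** The stated power and the success rule describe different events. The power statement covers each endpoint alone, with pain as a proportion and MME by the overall ANOVA. The rule asks for one and the same pair, Tukey-adjusted, on both endpoints, with pain as a score. The plan uses the both-endpoints requirement to justify no alpha adjustment across endpoints, but does not show what that rule does to power.

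The 80% is the only power figure in the article, so a reader is likely to take it as the chance of a positive trial and as covering all three dose comparisons. The second reading matters more. The 44 mg group is there to look for the balance between analgesia and motor function, and a non-significant result against either neighbour could be misread as equal analgesia if the comparison is thought to have 80% power.

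**Working it through.** **Inputs from Sample size estimation and Statistical analysis:** two-sided α = 0.05; pain rates 0.15/0.25/0.35; MME means 20/35/50, SD 12; n = 84 evaluable per group; Tukey over three pairs.

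**1. Reproducing the plan's figures.**
- *Pain, 84 per group.* A two-group comparison of 15% with 35% with continuity correction gives 83, and a three-group Wald test with unequal variances gives 83.3, rounded up to 84. Other routes do not match: 73 for the uncorrected pair, 91 for the three-group chi-square, 94 for the Tukey-adjusted 66 vs 33 mg pair.
- *Dropout.* 84/0.9 = 93.3, rounded up to 94. This agrees.
- *MME, 72 per group.* The one-way ANOVA noncentrality is n × [(−15)² + 0² + 15²]/12² = 3.125n. At n = 4 power is 76%; at n = 5 it is 88%. The printed inputs therefore need about 5 per group, not 72.

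**2. Three-group chi-square on pain at 84.** The mean rate is 0.25. Noncentrality = 84 × (0.10² + 0² + 0.10²)/(0.25 × 0.75) = 1.68/0.1875 = 8.96. On 2 df this gives 77% power; 91 per group are needed for 80%.

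**3. Tukey pairs on pain at 84.** The critical z is the studentised range 95% point for three groups divided by √2 = 2.344, a per-pair two-sided α of about 0.019. Power = Φ[(difference − 2.344 × pooled SE)/unpooled SE].

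| Pair | Difference | Pooled SE | Unpooled SE | z | Power |
|---|---|---|---|---|---|
| 66 vs 33 mg | 0.20 | 0.0668 | 0.0650 | 0.668 | 75% |
| 66 vs 44 mg | 0.10 | 0.0617 | 0.0612 | −0.729 | 23% |
| 44 vs 33 mg | 0.10 | 0.0707 | 0.0703 | −0.935 | 17% |

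By simulation, at least one pair is significant in 78% of trials.

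**4. Tukey pairs on MME at 84.** SE of a difference = 12 × √(2/84) = 1.852. The standardised differences are 15/1.852 = 8.1 for the adjacent pairs and 30/1.852 = 16.2 for 66 vs 33 mg, against a critical value of 2.36. Power is above 99.99% for every pair.

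**5. The written rule, pain as the dichotomy.** MME is practically certain to be significant for every pair, so the rule succeeds whenever any pain pair does: **about 78%**, and the pair powers in step 3 carry over unchanged. Simulation gave 78% at an assumed between-endpoint correlation of 0 and of 0.5. If nobody dropped out (94 per group) it would be 82% to 83%.

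**6. The written rule, pain as a score (assumption).** Take a normal score with equal SD in the three groups that crosses the cut-off in 15%, 25% and 35%. The normal quantiles are −1.036, −0.674 and −0.385, so the standardised differences are 0.65 (66 vs 33 mg), 0.36 (66 vs 44 mg) and 0.29 (44 vs 33 mg). Tukey power at 84 is 97%, 50% and 32%, and the rule as a whole has **about 97%**. Rounding to a 0–10 integer score (assumed SD 2) gives 96%. The 66 vs 33 mg pair falls to about 81% if its standardised difference is 0.5 and to 59% if it is 0.4. The article gives no figure that settles which applies.

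**The case against.** The strongest defence is that the sentence is literally a claim about each endpoint separately, so it never promised joint power. It can also be said that the rule concerns the NRS score, that a score carries more information than a dichotomy, and that under a plausible normal model the rule has about 97%. Both arguments stand as far as they go. They rule out a flat statement that the chance of a positive trial is below 80%.

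A reader might also infer that requiring two endpoints at 80% each must cost a great deal, for example 0.80 × 0.80 = 0.64 under independence. The documents do not support that. With the printed means and SD 12, MME power is about 100%, so requiring it as well takes nothing away. A large joint loss appears only if the printed 72 per group is taken at face value and an SD of about 57.6 is back-solved from it, 4.8 times the SD the article states. Nothing in the text supports that SD; the 72 simply does not follow from its inputs.

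The defence does not supply a power for the rule. The 97% depends on a distribution that the article does not give. Nor does it rescue the 44 mg contrasts, which stay at 50% and 32% even under that favourable model.

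**Conclusion.** The point holds in a limited form. The stated power does not belong to the stated success rule, and for the NRS score the rule's power cannot be derived because no mean or SD is given.

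On the only pain effect printed, with MME as printed, the rule has about 78% at 84 per group, 2 points under the stated level. That gap comes from the three-group or Tukey comparison on pain (77% even for the plain chi-square), not from adding MME. Under an assumed normal score the figure is about 97%, so a shortfall on the actual endpoint is not established.

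The firmer conclusion concerns the contrasts. Power comes almost entirely from 66 vs 33 mg. For 66 vs 44 mg it is 23% to 50%, and for 44 vs 33 mg 17% to 32%, depending on whether pain is treated as a proportion or as a normal score. These figures rest on the printed rates, SD 12 for MME and 84 evaluable per group.

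**What to change.** In Sample size estimation:

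1. State the NRS mean and SD assumed at 48 h in each group, so that the sizing refers to the endpoint that the rule tests.
2. Reconcile the MME means and SD with the printed 72 per group; as printed they give about 5.
3. Replace the per-endpoint claim with the simulated power of the success rule at 84 evaluable per group, that is, the probability that at least one pair is Tukey-significant on both endpoints. Give the correlation assumed between endpoints.
4. Give the same power for each of the three contrasts, so that the 80% is not read as applying to the 44 mg comparisons.

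The cost is a short simulation and a reworded paragraph. The stated power may become less favourable. N need not change.
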